## **SUMMARY OF THE MOST IMPORTANT GOALS OF THE PROJECT**

**PROPOSAL:** Gestational diabetes mellitus (GDM) is a growing health problem associated with adverse pregnancy and birth outcomes. It is also considered an established risk factor for the development of type 2 diabetes and cardiovascular disease over longer term for both women and the offspring. Its incidence is increasing, not only as a result of the application of more stringent criteria of diagnosing. In the last years, there has been a dramatic increase in the prevalence of prepregnancy obesity, a main risk factor for maternal and neonatal morbidity and mortality, as a direct consequence of the global obesity epidemic. Recent data suggest that the prevalence of obesity in reproductive-age women is around 10% in Spanish women. The origin of this epidemic is an unhealthy lifestyle, with high-energy and high-fat containing diets, physical inactivity and smoking. Of interest, there is now substantial evidence for the importance of the intrauterine environment on the health and longevity of the offspring, although the mechanisms underlying remain poorly understood. The Mediterranean Diet (MedDiet) has been associated with greater longevity and quality of life, and with potential advantages in the prevention of cardiovascular diseases. Thus, in this project we will attempt to study the effect of a lifestyle intervention based on a MedDiet and physical activity/exercise performance, beginning after the 1st gestational visit [8-12 gestational weeks (GWs)] and throughout the pregnancy, in the incidence of GDM rate. In addition, we will investigate its impact on genetic and epigenetic (DNA methylation and microRNAs expression) pattern expression, and gut microbiome composition both in women and in the offspring. Since GDM evolves through loops of deregulated inflammation, genetic/epigenetic modifications, gut microbiota and diet, we believe that the synergic analysis of such parameters could provide new biological insights and effective biomarkers that could have applications in prevention, molecular diagnosis and prognosis of GDM. The idea of preventing, or even managing, diseases such as diabetes or obesity with diet is very attractive but deserves further studies.

## **BACKGROUND**

Several modifiable risk factors related to the onset of type 2 Diabetes in women have been identified (1), and lifestyle changes, particularly the Mediterranean Diet (MedDiet), have proved to be effective in preventing its occurrence (2-3).

Gestational diabetes mellitus (GDM) is a growing health problem because of its increasing prevalence, its association with adverse pregnancy and birth outcomes (4) and because is an established risk factor for the development of type 2 diabetes and cardiovascular disease over longer term (5). The use of new criteria for diagnosing GDM, recommended after the HAPO study (6), has been associated with an increase in prevalence, i.e. from 8% (NDDG criteria) and 12.5% (Carpenter Coustan criteria) to 35% in a revaluation of our population of women (7). Despite the diagnosis of GDM with more stringent criteria, HAPO study shows a continuous association of maternal glucose levels below those previously used to GDM diagnosis with increased birth weight and adverse pregnancy outcomes. Regarding this dramatic increase in GDM diagnosis observed with the proposed IADPSG criteria, it is important to remember that previous criteria required two abnormal oral glucose tolerance tests. However, it has been demonstrated that women who had one abnormal test value and who were considered previously as "normal" had many of the outcomes that were similar to those who were as GDM.

Recently, based in a large population of more than 2000 women, our group has developed a risk appraisal model for GDM by identifying modifiable factors that can help to predict the risk of GDM (7). After logistic regression model, biscuits and pastries <4 times/week, red and processed meats intake < 6 serving/week, juices < 4 servings/ week, light walking >30 minutes/day and 30 minutes/day of physical activity of moderate intensity at least 2 days/week was associated with less GDM risk compared to the opposite. This data may represent a promising approach for the prevention of GDM and subsequent complications. In Spain, the Community of Madrid is one of the regions with higher foreigner rates, 18.8% of the total population (January 2011), with 49.7% of women. About 50% of pregnant women attended in our hospital during 2012 were immigrants. Recently, we have reported that this population tends to acquire the same risk factors as the Spanish population associated with lifestyle (8). Prepregnancy

8. Pérez-Ferre N et al. Effect of lifestyle on the risk of gestational diabetes and obstetric outcomes in immigrant Hispanic women living in Spain. *J Diabetes* 2012;4:432-8
9. Guelinckx I et al. Maternal obesity: pregnancy complications, gestational weight gain and nutrition. *Obes Rev* 2008;9:140-50
10. Vrachnis N et al. Role of adipokines and other inflammatory mediators in gestational diabetes mellitus and previous gestational diabetes mellitus. *Int J Endocrinol* 2012;54:9748
11. Metzger BE. Long-term outcomes in mothers diagnosed with gestational diabetes mellitus and their offspring. *Clin Obstet Gynecol.* 2007;50(4):972-9

**STUDY HYPOTHESIS:** Traditionally, it has been widely accepted that genetic and adult lifestyle factors determine our risk of developing some diseases such as obesity, diabetes and cardiovascular disease in later life. However, there is now substantial evidence of the importance of the intrauterine environment in determining our susceptibility to such diseases in later life, although the mechanisms underlying remain poorly understood. In addition, one cannot consider genetic determinants of human metabolism without considering the influence of dietary components metabolized by gut microbiota. Therefore, in this project we have hypothesized that a lifestyle intervention based on the MedDiet and physical activity/exercise performance, beginning after 1st gestational visit [8-12 gestational weeks (GWs)] and throughout the pregnancy, will reduce the incidence of gestational diabetes mellitus (GDM) in women with normal fasting plasma glucose (FPG). Moreover, the mechanism by which MedDiet/physical activity could alter long term disease risk in both women and their offspring may involve epigenetic processes or alterations in gut microbiome composition.

## **OBJECTIVES:**

### **Primary outcome:**

- To define the prevention of GDM (evaluated at 24-28 GWs with HAPO criteria) after the lifestyle intervention based on MedDiet and physical activity/exercise, as compared to standard treatment, in women with normal FPG (<92mg/dL) at the 1st gestational visit (8-12 GWs).

### **Secondary outcome:**

- To define functional genetic risk of developing GDM focusing in obese and non obese pregnant women.
- To investigate the effects of MedDiet and physical exercise/activity scheduled in inflammatory biomarkers in pregnant women.
- To investigate the effects of MedDiet and physical exercise/activity scheduled in the epigenetic mechanisms (DNA methylation and miRNA expression) in pregnant women and offspring; if so, it would represent a novel epigenetic mechanism for regulation of gene expression in the offspring.
- To investigate whether the MedDiet and physical exercise/activity scheduled alters the composition of the gut microbial flora both in women and offspring.
- To evaluate the impact of all these parameters on the long-term health of newborns in the first year of life.
- To estimate changes in HbA1c, insulin, HOMA, lipid profile, body weight, blood pressure, adherence to changes in lifestyle estimated by Med Score and urinary hydroxytyrosol levels and plasma  $\gamma$ -tocopherol levels to confirm compliance in the group receiving MedDiet [extra virgin olive oil (EVOO) and pistachios].
- The parameters to be assessed will be: gestation duration and fetal development; delivery characteristics such as caesarean delivery and instrumental vaginal birth, placental weight; and newborn data such as newborn weight, Apgar test values and cord blood pH.

### **Summary Intervention**

Strategies for preventing GDM have until now been focused on diet and exercise interventions, which have had mixed results. This could be possibly because many of these trials have studied small sample sizes. A recent randomized controlled trial of MedDiet intervention (PREDIMED Study) has reported a decline in fasting plasma glucose [-7 (IQR:-13; -1.3) mg/dl] after 3 months in a Mediterranean population at high cardiovascular risk. These data could represent a potential reduction of GDM rate of more than 30%, although this aspect deserves to be demonstrated. The project proposed is a large, prospective, randomized, clinic-based, interventional study with two parallel groups that will provide to answer this question.

### **SAMPLE SIZE CALCULATION**

For sample size calculation, a primary end-point for conversion to GDM has been used, assuming an expected conversion rate of 35% between 24-28 GWs and a reduction of at least 30% in the conversion to GDM after intervention. This intervention has shown a decrease of FPG -7 (-13; -1.3) mg/dl after 3 months in the PREDIMED Study (1), representing a potential reduction of GDM rate higher than 30%. A sample size of 315 women analyzed per group to provide statistical power of 80% to detect a 30% difference between groups in the primary outcomes at 5% significance. This number has been increased to **500 per group**, to allow for a predicted drop-out of around 20% (in accordance with the expected response rate, loss to follow up, lack of compliance, and any other predicted reasons for loss of subjects). Therefore, **1000 women will be randomized** in the study and we expect to assess at least 700.

### ***Selection of Patients***

The Institutional Review Board and the Clinical Ethic Committee of the Hospital Clínico San Carlos have approved this protocol before initiation of the study (approval reference: CP.CI.13/296-E). We will include pregnant women who fulfill the inclusion criteria and none of the exclusion criteria. Subjects must give signed and dated informed consent (attached in a separate file) prior to any trial-related activities. Structure of the trial is displayed in ***Figure 1***.

Inclusion criteria: women >18 year old, with normal fasting glucose values (< 92 mg/dl) in the 1st gestational assessment (8-12 GWs) and sign the informed consent.

Exclusion criteria: women with fasting glucose levels  $\geq 92$  mg/dl in the 1st gestational assessment (8-12 GWs), multiple pregnancy, nut allergy, or any other reason, medical condition, ongoing medication or significant disability that would prevent the participant complying with trial consent, treatment and follow-up procedures or potentially jeopardize her medical care.

Figure 1 - Flowchart of the trial.

[figure not shown]

### Intervention

Eligible women will randomly be assigned to the:

- **Control group (CG).** Women will be assigned to a standard treatment based on recommendations provided in clinical practice. The main recommendation is to reduce all types of fat from both animal and vegetable sources including nuts and EVOO, and a training program is also provided. This prudent diet recommendation represents a contribution of total fat less than 30% of total energy intake (<40 mL EVOO and not nuts consumption), and carbohydrate intake more than 50%. Women will be followed up by the Obstetric Department.
- **Intervention group (IG).** Women with free allotments of EVOO (1 liter/week) and pistachios (150 g/week), and the training program. Dieticians will give personalized

dietary advice to participants with instructions directed to use of EVOO for cooking and dressing, increased consumption of fruit, vegetables, legumes, and fish and avoidance of red or processed meat, butter, cream, fast food, sweets, pastries, and sugar-sweetened beverages. This intervention diet is comprised of an intake of approximately 35-40% of total fat (predominantly unsaturated fatty acids) and 40-45% of low glycemic index carbohydrates, maintaining a protein intake of 20%, similar to the control diet. Nutrition intervention is aimed to achieve a lifestyle score >10 or Nutrition Score >8 based on Diabetes Nutrition and Complications Trial (DNCT) previously reported. The questionnaire is displayed in **Table 1**. Women will be followed up by the Endocrinology Department.

The main investigator will construct a Master Randomization List using a permuted block design. Women will be stratified by age, BMI and parity and allocation will be assigned in a ratio of 1:1 in random blocks of 4 and 6.

### ***Follow-up***

Women will be enrolled at 8-12 GWs (visit 0) and will follow-up at GWs 12-14 (visit 1), 24-28 (visit 2), 34-36 (visit 3) and delivery (visit 4), as well as at 12 weeks (visit 5) and 1 year post delivery (visit 6).

Baseline assessments (Visit 0): Women will be evaluated after the signature of the informed consent form. A complete medical history and physical exam will be performed. Subsequent assessments (Visits 1-6): Women will be followed up by means of clinic visits by the study staff. Six clinic visits will be performed, including: assessment of endpoints/outcome measures, assessments of safety including general (e.g. physical examination), specific safety assessments (e.g. blood chemistries including general biochemistry, hematology and urine analyses) and adverse event collection, assessment of compliance with the study and recording of concomitant medications. Blood and stool samples will be taken at this time. At visit 5 and 6, cord blood and placenta will be taken.

All biological samples will be extracted in one point and will be supervised by a scientist staff that will ensure fit for-purpose operations (high-throughput, high-quality). Design and testing of the sample-handling protocol will consider key factors that could affect the stability of biological samples, including anti-coagulants, stabilizing agents, temperature, and elapsed time from collection to initial processing and endogenous

degrading properties (enzymes). Sample fractions will be stored in two separated ultra-low temperature freezers to ensure long-term stability and integrity.

## GDM TREATMENT

Women from both groups diagnosed with GDM will be referred to the Diabetes and Pregnancy Unit and treated according to local guidelines previously reported (The St. Carlos Gestational Diabetes Study. *Diabetes Care* 2014;37:2442-50). **Figure 2** shows a flowchart of GDM treatment protocol.

Lifestyle intervention: Specific diet was not provided to the women, just some recommendations on Lifestyle. Women will be advised to avoid or limit the intake of refined carbohydrates, sugary drinks including fresh fruit juices, red meat (particularly processed meat), bakery and pastries. At least 3 servings of skimmed dairy products per day, 2 servings of vegetables per day, and 2 servings of fresh fruit (excluding juices) per day will be recommended. Nuts instead of processed meat snack; oily fish and EVOO daily; and whole grain cereals and legumes instead of white cereals and potatoes will also recommended.

A physically active lifestyle including walking at least 15 minutes, and climbing stairs at least 4 floors, 4 times a day > 5 days per week, will be recommended.

A semi quantitative questionnaire was used to collect lifestyle adherence to these recommendations and displayed. The goal will be to achieve score >8

Figure 2 - GDM treatment.

[figure not shown]

## TEAM.

The Department of Endocrinology and Metabolic Diseases of the Hospital Clínico San Carlos is a leading research group in the field of prevention and epidemiology of diabetes in Spain. Its personnel have been involved in various landmark projects on public health aspects of diabetes, and cardiovascular diseases, in Spain and in many other countries. In the last years, the group has developed an interest in GDM, establishing a close collaboration with the Department of Gynaecology and Obstetrics of the Hospital Clínico San Carlos.

In this project, each gynaecologist/obstetric investigator will be responsible for recruiting patients, asking for and obtaining written informed consent, evaluating inclusion and exclusion criteria and notifying the patient inclusion to the coordinator. They will also be responsible of random group assignment, program patient visits according to the study protocol and data collection. For this task, age, sex, education level (no studies, elementary, secondary, technical school or university graduate), marital status (single, divorced, married or living together as a couple or widowed) smoking habits (current vs. non-smoker), leisure-time sports (days per week and hours per day), family history of diabetes or metabolic syndrome, personal obstetric history and history of hypertension, dyslipidemia or coronary heart disease will be recorded. Weight, height and waist and hip circumferences will be directly measured by the research physician using standardized methods. Since women who developed GDM will need intensive blood sugar control to prevent maternal and fetal complications and treatment with dietary or medication therapy based on their individual needs, endocrinologists will follow them. They will be simultaneously followed by their obstetricians for appropriate monitoring of the pregnancy. A dietician will carry out lifestyle interventions for all women. They will be developed during a 1-h session (Visit 1) for each woman individually and will be reinforced at each follow-up visit. We have developed a questionnaire to evaluate adherence to recommended lifestyle changes (*Table 1*). A score of +1, 0 or -1 has been assigned to each of the 18 items on the questionnaire, with a value of +1 indicating that the beneficial recommendation is regularly performed, -1 indicating that the beneficial recommendation has not been adopted or that patients are persisting with an unhealthy habit, and 0 indicating

intermediate consumptions or exercise frequency between healthy and unhealthy adults. Different composite variables from the questionnaire will assess overall Lifestyle, including a Physical Activity score (items 1 -3), a Nutrition score (items 4 -15), a Low Glycaemic Index score (items 4, 5, 9, and 10), an Unsaturated Fat score (items 6 -8).

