| 7. How many sweet or carbonated beverages do you drink per day?                                                                        | <1                                |
| 8. How much wine do you drink per week?                                                                                                | ≥7 glasses                        |
| 9. How many servings of legumes do you consume per week? (1 serving : 150 g)                                                           | ≥3                                |
| 10. How many servings of fish or shellfish do you consume per week? (1 serving 100–150 g of fish or 4–5 units or 200 g of shellfish)   | ≥3                                |
| 11. How many times per week do you consume commercial sweets or pastries (not homemade), such as cakes, cookies, biscuits, or custard? | <3                                |
| 12. How many servings of nuts (including peanuts) do you consume per week? (1 serving 30 g)                                            | ≥3                                |
| 13. Do you preferentially consume chicken, turkey, or rabbit meat instead of veal, pork, hamburger, or sausage?                        | Sí                                |

|                                                                                                                                                                                            |    |
|--------------------------------------------------------------------------------------------------------------------------------------------------------------------------------------------|----|
| 14. How many times per week do you consume vegetables, pasta, rice, or other dishes seasoned with sofrito (sauce made with tomato and onion, leek, or garlic and simmered with olive oil)? | ≥2 |
|--------------------------------------------------------------------------------------------------------------------------------------------------------------------------------------------|----|

*Natural fruit juice and alcohol consumption will not be accounted for. Adapted from Martínez-González MA et al.*

*PLoS ONE. 2012; 7(8): e43134.*

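### The lifestyle and MEDAS scores measure likeness to the intervention diet, not adherence to each arm's own advice, and for nuts they run backwards in the control group

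*Protocol*

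**What the plan says.** The Protocol's list of secondary outcomes includes "adherence to changes in lifestyle estimated by Med Score", with biomarkers to confirm compliance in the group receiving the Mediterranean diet. The Team section gives the purpose of the Table 1 instrument: "We have developed a questionnaire to evaluate adherence to recommended lifestyle changes". Each item is scored +1, 0 or −1, the lowest mark being minus "1 indicating that the beneficial recommendation has not been adopted or that patients are persisting with an unhealthy habit". There is one key with no arm-specific version, and the text below Table 1 has lifestyle data collected from all women.

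The two arms receive opposite advice on two of the scored foods. For the control group (CG), the Intervention section states: "The main recommendation is to reduce all types of fat from both animal and vegetable sources including nuts and EVOO". It quantifies this as "<40 mL EVOO and not nuts consumption". The May 2017 addendum repeats both statements. The intervention group (IG) is described as "Women with free allotments of EVOO (1 liter/week) and pistachios (150 g/week".

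The November 2014 addendum adds the 14-point MEDAS. Its item 2 gives a point for at least 4 tablespoons of olive oil a day. Item 12 asks "How many servings of nuts (including peanuts) do you consume per week? (1 serving 30 g" and gives a point for 3 or more.

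**The concern.** A measure called adherence to recommendations should rise when a woman does what she was told. For nuts in the CG it falls: the woman who obeys is recorded as not having adopted the recommendation, and the woman who ignores her advice and eats nuts often is recorded as having adopted it.

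Two misreadings follow. A low CG score may be reported as poor adherence in the control arm when it partly reflects good adherence to the control advice. A CG score raised by nuts or generous EVOO may be reported as good adherence when it is contamination, which would weaken the contrast on gestational diabetes (GDM). In addition, some of any between-arm difference in the total follows from the assigned advice and the free supply. The total alone does not separate this from wider dietary change in the IG.

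**Working it through.** The plan gives no expected value or target difference for this outcome, so there is no figure to reproduce. The check adds up the scoring rules for two women who each comply fully and are alike on all other items.

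**Inputs**
- Table 1, item 6 (nuts, weekly): +1 above 3, 0 for 1–3, −1 below 1.
- Table 1, item 7 (EVOO, weekly count, no volume): +1 above 6, 0 for 3–6, −1 below 3.
- MEDAS item 2: 1 point for ≥4 tablespoons a day. Item 12: 1 point for ≥3 servings of 30 g a week.
- CG advice: no nuts, EVOO below 40 mL. IG supply: pistachios 150 g/week, EVOO 1 L/week.
- Assumptions: the 40 mL limit is per day (no time unit is stated), a tablespoon is 10–15 mL, and the IG woman eats the pistachios, uses EVOO on more than 6 occasions a week and takes at least 4 tablespoons a day.

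**Nuts**
- IG: 150 g ÷ 30 g = 5 servings a week, hence +1 on Table 1 and 1 on MEDAS. Table 1 states no serving size; +1 holds for any unit below 150 ÷ 3 = 50 g.
- CG: 0 a week, hence −1 on Table 1 and 0 on MEDAS.
- Gap: +1 − (−1) = 2 on Table 1; 1 − 0 = 1 on MEDAS.

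**EVOO**
- MEDAS: 4 tablespoons = 4 × 10 to 4 × 15 = 40 to 60 mL, so an intake below 40 mL always scores 0. The IG supply is 1000 ÷ 7 = 143 mL/day, so the point needs 40 ÷ 143 = 28% to 60 ÷ 143 = 42% of it. Gap: 1.
- Table 1: a CG woman taking 30 mL daily is within the limit and counts 7 uses a week, hence +1 and a gap of 0. The gap is 2 only if she uses EVOO fewer than 3 times a week.

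| Score | Obedient CG vs IG gap | Range of score | Share of range |
|---|---|---|---|
| Nutrition (items 4–15) | 2 to 4 | −12 to +12 (24) | 2/24 = 8% to 4/24 = 17% |
| Unsaturated Fat (items 6–8) | 2 to 4 | −3 to +3 (6) | 2/6 = 33% to 4/6 = 67% |
| MEDAS | 2 | 14, or 13 without the wine item | 2/14 = 14% or 2/13 = 15% |

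In the Unsaturated Fat score the obedient CG woman's ceiling is −1 + 1 + 1 = +1 with frequent EVOO, or −1 − 1 + 1 = −1 with rare EVOO. The IG ceiling is +3.

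**Total score.** The stated goal, set for the nutrition intervention, is Lifestyle above 10 or Nutrition above 8. The best obedient CG score is Nutrition 12 − 2 = 10 and Lifestyle 15 − 2 = 13 with EVOO at +1, or Nutrition 8 and Lifestyle 11 with EVOO at −1. She can reach the goal in either case. (Table 1 and the sub-scores show 15 items; the Team section says 18. The 15-item version is used here.)

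**The case against.** The strongest reply is that the construct is adherence to the Mediterranean diet. One tool carries that name, the key speaks of a beneficial recommendation and not of the advice given to a woman's own arm, and the biomarkers are named to confirm compliance in the Mediterranean diet group. On that reading, a gap on nuts and EVOO is the exposure contrast the trial was built to create, and a score of uptake should include those foods. This stands. It defends the full score as a measure of separation between arms, but not its use as adherence in women who were told the opposite.

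Further points limit the concern:
- A reader might infer that an obedient control woman is classed as non-adherent. The document sets no cut-off for the CG, and she can exceed the IG goals. The reversal is at item level. Free supply also scores nothing; only reported intake does.
- A reader might infer that EVOO is reversed on Table 1 as well. That item counts occasions and the CG limit is a volume, so no gap is forced.
- A reader might infer that dietary change beyond the supplied foods cannot be seen. The Low Glycaemic Index score (items 4, 5, 9 and 10) already excludes nuts and EVOO.
- A reader might infer that contamination is hidden. Controls eating these foods would narrow the gap, and biomarkers are measured in a random 10% of both arms at baseline and at 24–28 weeks. What is missing is a reading of these data as contamination.
- After a GDM diagnosis both arms are advised nuts and daily olive oil, so the conflict does not apply to those control women from then on.

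**Conclusion.** The concern holds in a limited form. Table 1 and MEDAS measure likeness to the IG diet. For nuts, both score a control woman's obedience as the unfavourable answer, and MEDAS item 2 does the same for olive oil. The sizes calculated above are ceilings for full compliance in both arms, not predictions of the observed difference. They rest on a daily reading of the 40 mL limit, 10–15 mL per tablespoon, and IG women consuming the supplied foods as assumed. The Unsaturated Fat score is the most affected, since two of its three items are supplied foods.

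The conflict concerns control women before, or without, a GDM diagnosis. It would be wrong to infer a bias in the primary result: the GDM comparison and the sample size do not use these scores. Severity is minor; the fault lies in the label and the interpretation.

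**What to change.** 1. Describe the outcome as a Mediterranean diet score, and state that it is not to be interpreted as adherence in the control arm.
2. Keep the full score, and also report the between-arm comparison without the supplied-food items: Table 1 items 6 and 7, and MEDAS items 1, 2 and 12.
3. Report the control-arm distribution of the nuts item (the three Table 1 bands and MEDAS item 12) together with the control-arm biomarkers as the measure of contamination. Add olive-oil intake if raw amounts were recorded.

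A share of controls meeting both limits exactly should not be promised from the scored items. The lowest Table 1 nuts band is below 1 a week and not zero, its EVOO item has no volume, and MEDAS item 2 is cut at 4 tablespoons (40–60 mL), which need not coincide with 40 mL.

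The cost is a little extra tabulation of items already collected, and a probably smaller reported difference once the supplied foods are removed. No treatment, visit or primary analysis changes.
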